### Variables

**
*Phase 1 A: Prospective longitudinal cohort study*.** The main outcome is to define the characteristics of multimorbidity. We will employ enhanced point of care test (POC) diagnostics for patients admitted to the study to determine the prevalence of multimorbid diseases of interest (specifically HIV, hypertension, diabetes and chronic kidney disease). All POCs used in the study are CE marked and commercially available. We will make the results of these tests available to treating healthcare providers using a standardised proforma. No treatment recommendation will be provided with this information and clinicians will be able to interpret and use this information independently. Structured data extraction of clinical information (including potential predictors of patient outcomes) will be performed at intervals (described in
Table 1 from patient records.

**
*Phase 1 B: Health economic evaluation*.** To explore the impact of socioeconomic status (SES) on patient costs, clinical outcomes and health-related quality of life (HRQoL) we will calculate wealth scores and use these to assign all clinical cohort study participants to SES quintiles. For participants randomised to the health economic study, we will collect data on patient costs at admission (in person), discharge (in person), 30 and 90 days post discharge (in person or by telephone). Health system costs for patients in the cohort study will be modelled using top down and bottom up costing methods. HRQoL will be estimated in quality adjusted life years (QALYs).

**
*Phase 1 C: Situation analysis*
** In depth interviews (IDI) and focus group discussions (FGD) with patients recruited to the cohort study, and their care givers will be conducted to understand their experiences, preferences, and priorities, including level of health literacy and engagement with healthcare providers for long term management of chronic conditions. Exploration of detailed experiences from patients and carers will provide specific concrete examples of their expectations, and any concerns they have, as well as their priorities and perceptions of how the hospital currently manages acute medical patients with multimorbidity, problems and how best to address them.

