Other conditions are expected to contribute to multimorbidity, for example hearing and visual impairment, causes of impaired mobility such as injury at birth, or disability from trauma, surgical procedures and others later in life. A key criterion for inclusion in the planned intervention study will be potential for improved morbidity or mortality from linkage to care. We will therefore collect data on disability using standardised questionnaires, with key components from Washington Group on functioning, Patient Health Questionnaire (PHQ)-9 for depression in addition to data tools used in previous cohort studies for the collection of standardised clinical information, and allow this to inform the intervention design.

Clinical outcomes, coded from a structured case summary and the available medical notes, will be established as follows:

1.Medical diagnosis and supporting evidence.2.In-patient treatment of these diagnoses, including time of appropriate treatment establishment.3.Vital signs, including pulse oximetry (using a A310 finger oximeter), respiratory rate, pulse rate, blood pressure and temperature.4.Routine laboratory data supporting these diagnoses (such as urine lipoarabinomannan [LAM], serum CrAg).5.Clinical outcomes will also be ascertained at hospital discharge, 30 days and 90 days as:6.Death (coded from all available records).7.Readmission to hospital.

Data will be collected by a study nurse using electronic data capture. This will describe the patient characteristics, medical history and ‘patient journey’ through the healthcare system. Age, date of birth and sex will be documented from patient reports and/or clinical notes. To ensure complete data collection, we will prospectively collect data on vital signs, details of resuscitation, medication administration, results of clinical, laboratory, and radiologic examinations. All clinically relevant findings will be entered into the medical notes to ensure availability to the responsible clinicians.

As a component of the functional assessment, we will measure hand grip strength at day 90 follow-up using a GRIPX Digital Hand Dynamometer, which is a known predictor of health and overall strength
^
28
^. Grip strength will be measured seated on a chair without elbow rests, with the elbow loosely flexed at 90
^0^, and the wrist in a neutral position
^
29,
30
^. Grip strength will be measured as the mean of three tests on both hands with 60 seconds of recovery between each attempt.

**

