*Phase 1 B: Health economic data sources and measurement*.** All consenting study participants will be asked asset ownership, house construction and demographic questions extracted from the most recent relevant national Demographic and Health Survey (DHS). Patient cost data will be captured before, during, and for 90 days after hospital admission using an amended version of the STOP-TB tool, a widely-used questionnaire for measuring TB patient costs
^
31
^. We will capture direct medical costs (
*e.g.*, drugs, diagnostics, consultation and inpatient fees), non-medical costs (
*e.g.*, food and transport), indirect costs (lost time for patients and guardians). Where a patient is readmitted to hospital, we will also capture these costs. Costs will be captured in local currency and presented in 2024 United States dollars.

Health system costs will be collected using top-down and bottom-up (micro) costing methods. We will develop and validate (with relevant hospital staff) a visual model of individual patient pathways through the study hospitals. This will be supplemented with data on waiting times, and time spent with various health workers from the sample of patients that are included in observations conducted as part of the situation analysis. Costs for each stage of the patient pathway (triage, admission, diagnostics, treatment, discharge, readmission
*etc*.) will be based on unit costs for tests, staff time, hospital bed days and other inputs, obtained from hospital data, tests and consumables suppliers, and Ministry of Health (MoH). Any other costs deemed relevant during the data collection stage will also be included. Top-down costing data on hospital overheads (utilities, building costs, maintenance,
*etc*.) will be obtained for each hospital.

HRQoL data will be collected using the EQ-5D-5L questionnaire in English, Chichewa (Malawi) and kiSwahili (Tanzania). The questionnaire will be administered, at admission, discharge, 30 and 90 days post admission in person or (day 30) by phone (as for patient costs).

**

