### Sample size

**
*Phase 1 A: Prospective longitudinal cohort study*.** The primary outcome will be disease prevalence. At 5% prevalence, a precision of 1.5% and power of 90% at α=0.05 is expected (precision will reduce as actual estimate rises towards 50%). We will use 5% prevalence as the lower boundary for inclusion of the disease during intervention development. We expect that HIV, hypertension and diabetes will meet this threshold. The cohort will allow us confidence to decide on the inclusion of chronic kidney disease. Prevalence will be assessed in both countries at the district and central hospital level to determine if findings are shared across settings. Given these assumptions, sample size is 1544 patients, with a target of 1600 to account for drop out. We will recruit these patients across the four hospitals (with numbers varying between sites due to different patient loads).

**
*Phase 1 B: Health economic evaluation*.** A randomised sub-sample of one third of the cohort study participants will be selected for participation in patient costing and HRQoL analysis (approximately 133 participants per hospital).

**
*Phase 1 C: Situation analysis*.** Sampling strategies for patients and caregivers is designed to include those individuals representing: those admitted for the first time and those who are returnees; those on HDU, ICU and ordinary wards; different age categories; male and female. We will ensure inclusion of patients with multiple known pathologies representing “multimorbidity” according to the final definition. Sample sizes for interviews are preliminary; they will continue until a point of saturation is reached.
Table 2 shows estimates of the number of patient and carer interviews required. For healthcare workers, we will include different cadres working in different departments.

**Table 2. T2:** Number of in-depth interviews, focus group discussions and structured discussions.

PER HOSPITAL SITE	In-depth interviews	Focussed group discussions	Structured discussions
Patients with multimorbidity *	10	24	10
Caregivers to patients with multimorbidity *	10	24	10
Doctors	2	-	4
Nurses	4	-	8
Ward attendants	2	-	6
Reception / frontline administration staff	2	-	2
Total	30	48	40

* Patients and caregivers will not be the same group during IDIs and FGDs. IDI, In depth interviews; FGD, focus group discussion.

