*e.g.*, lost time for paid or unpaid work, including housework) will be estimated based on the number of days of reported inability to work multiplied by the pre-disease wage given by patients during their baseline interview. The patient pathway model will be parameterised with unit costs and used to estimate individual patient and health system costs for a set of the most frequently observed multimorbidity combinations and patient types. Capital costs extending beyond one year will be annualised over their expected lifespan. Results will be presented as means and 95% confidence intervals. Deterministic and probabilistic sensitivity analyses will be conducted to test the robustness of the results. Multiple logistic regression will be used to compare patient costs by multimorbid condition(s) and wealth quintile to identify any significant differences. Additionally, we will examine the relationship between patient costs and age and sex. Change in HRQoL, expressed as QALYs, between admission, day 30 and day 90 interviews will be estimated using the area under the curve method. QALYs will be calculated according to the most relevant available tariff based on both geographical proximity and economic context. In our study we will use Uganda’s tariff for Tanzania, and Zimbabwe’s tariff for Malawi. Updated tariffs will be used if these become available before the analysis. The QALY calculations will also consider mortality during follow-up by attributing the lowest value from each value set (which corresponds to death), from the date of death until the end of the follow-up period. Missing patient cost or HRQoL data will be imputed using multiple chained imputations modelling with a predictive mean matching algorithm and relevant baseline variables.

Health economic analysis will be performed in Stata v15.4 and Excel.

**
*Phase 1 C: Situation analysis*.** Transcription and translation will be performed in line with local standard procedures. For accuracy, during the first 10 transcriptions a researcher will read the transcribed interviews and focus groups while listening to the audio recordings, and then check translations. Further checks will depend on the quality of these initial evaluations.

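### Mean 90-day QALYs are planned from a random third of the cohort, with no stated use of the deaths followed in everyone, so their interval is wider than the collected data allow

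*Protocol article*

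**What the plan says.** All references are to the protocol article.

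- **Who is analysed.** Sample size, Phase 1 B: "A randomised sub-sample of one third of the cohort study participants will be selected for participation in patient costing and HRQoL analysis", put at "approximately 133 participants per hospital". The cohort target is in the Phase 1 A paragraph: "sample size is 1544 patients, with a target of 1600 to account for drop out".
- **What is collected only in the third.** Variables, Phase 1 B: "For participants randomised to the health economic study, we will collect data on patient costs at admission", then at discharge, 30 and 90 days.
- **What is collected in everyone.** Wealth data serve to "assign all clinical cohort study participants to SES quintiles", and Data sources and measurement, Phase 1 B, adds: "All consenting study participants will be asked asset ownership, house construction and demographic questions". For the clinical cohort: "Clinical outcomes will also be ascertained at hospital discharge, 30 days and 90 days as" death and readmission. Hospital, age and sex are also recorded.
- **How results are summarised.** Analysis, Phase 1B: "Results will be presented as means and 95% confidence intervals". QALYs come from the area under the curve. From the date of death to the end of follow-up, a participant receives the lowest value of the relevant value set. Malawi and Tanzania use different tariffs.
- **Missing data.** The same section imputes missing cost or HRQoL values by chained equations from baseline variables. It does not mention death or readmission as predictors.
- **Timing.** Study status says that follow-up is under way and analysis has not been performed.

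**The concern.** The economic study is a random second-phase sample inside a cohort that carries strong predictors of its outcome. Death is the clearest case. Once a participant dies, the rest of that participant's QALY is set by rule, and death is followed in all participants. As written, the mean QALY depends only on the deaths that happen to fall in the third. A chance excess or shortage of deaths there passes straight into a primary health economic estimate.

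Two things are at stake. The QALY interval is wider than the collected data allow. The mean QALY also embeds a mortality that can differ, by chance, from the figure the cohort itself reports. The imputation model adds to this: if it holds baseline variables only, it leaves out post-admission events that bear strongly on the missing values.

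**Working it through.** **Step 1: the plan's own figure.** 1600 × 1/3 = 533.3, and 533.3 / 4 = 133.3 per hospital. This reproduces the stated figure as an average over four hospitals.

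**Step 2: formula.** Take a simple random second-phase sample of n from N. A regression or calibration estimator of the mean then has, relative to the sub-sample mean,

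variance ratio = 1 − R²(1 − n/N)

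where R² is the share of outcome variance explained by variables known in all N. With n = 533 and N = 1600, 1 − n/N = 0.667, so the width ratio is sqrt(1 − 0.667 R²). The equivalent sample size is 533 divided by the variance ratio.

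**Step 3: range of R²** (not in the document, so assumed).

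| R² | Variance ratio | Width ratio | Narrower by | Equivalent n |
|---|---|---|---|---|
| 0.1 | 0.933 | 0.966 | 3% | 571 |
| 0.3 | 0.800 | 0.894 | 11% | 666 |
| 0.5 | 0.667 | 0.816 | 18% | 800 |
| 0.7 | 0.533 | 0.730 | 27% | 1000 |

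Using 1544 and 515 instead gives the same width ratios to within 0.001.

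**Step 4: plausible R² for QALYs.** Simulation with 3000 replicates per scenario, all inputs assumed: time to death exponential with mean 25 days, cut at 90; utility while alive with mean 0.65 and SD 0.2, constant over time; death valued at 0. The regression used death, days alive, length of stay, readmission and wealth.

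| 90-day mortality | R² | SE ratio |
|---|---|---|
| 10% | 0.40 | 0.86 |
| 20% | 0.57 | 0.78 |
| 30% | 0.67 | 0.74 |
| 40% | 0.73 | 0.73 |

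Both estimators had the same average, so no bias was visible. The range is 14–27% narrower, equivalent to 533/0.86² ≈ 720 up to 533/0.73² ≈ 1000 participants.

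**Step 5: patient costs.** The same simulation with a skewed cost gave R² of about 0.11 and SE ratios of 0.97–0.98. A second simulation, with cost driven by stay, readmission and in-hospital death (R² about 0.30), gave SEs of 3.39 and 3.17, a ratio of 0.94. That is a smaller gain than the 0.894 the formula gives at R² = 0.30. The gain for costs is about 2–6%, and both simulations had length of stay available.

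**Step 6: incomplete day-90 status.** Replace N by the number with known status. If that is 1544 with 533 still in the third, 1 − 533/1544 = 0.655. At R² = 0.5 the width ratio is then sqrt(1 − 0.327) = 0.820 rather than 0.816. Heavier loss would cost more.

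**The case against.** **The planned mean is not wrong.** The mean of a random third is unbiased and its interval has proper coverage. A difference between mortality in the third and in the cohort is ordinary sampling variation that the interval already covers. This stands: a reader might infer bias, and the document does not support that.

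**The estimator may be settled elsewhere.** The sentence on means and intervals is a reporting format. It does not exclude weighting, and an analysis plan may exist. This stands in part. The article does, however, fix the analysis set at one third and name baseline variables for imputation, so what is written points away from using cohort-wide outcomes.

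**The cohort data are incomplete.** Limitations says that CKD needs evidence at three months and is open to survivorship bias. The recruitment target allows for drop-out. Length of stay is not named as a variable. All of this stands; it shortens the calibration list and trims the gain.

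**Stronger readings that do not hold.**

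- *EQ-5D was given to everyone.* Table 1 schedules it without limiting it to the third, and full collection would give a width ratio of sqrt(533/1600) = 0.58. But Table 1 lists patient costs without a limit too, and Variables confines those to the sub-sample. A missing limit in that table therefore proves nothing.
- *A very large QALY gain.* With 15% in-hospital and 10% post-discharge mortality and death valued at 0, one simulation gave R² of about 0.80 and a ratio of 0.67. That lies outside the 0.73–0.86 found in Step 4, and I do not rely on it.
- *A material gain for costs.* Neither simulation supports it.
- *Unequal sampling fractions.* A reader might take 133 per hospital as a quota while recruitment varies by site. The figure reproduces as an average, and the text says one third, so a quota is not established.

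**Conclusion.** The point holds as an avoidable loss of precision in mean 90-day QALYs, not as an error or a source of bias. Interval width could be multiplied by sqrt(1 − (2/3)R²). For QALYs a reduction of about 14–27% is plausible, resting on assumed mortality of 10–40%, the assumed utility distribution, death valued at 0 and complete day-90 status. The plan instead values death at the lowest point of each tariff, so the size will shift. The simulated gain also used days alive; knowing only whether a participant had died would recover less. For patient costs the gain is small, about 2–6%. Health system costs are modelled separately and are not affected.

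It is worth acting on because HRQoL change is part of the primary health economic objective, the data are being collected anyway and the analysis has not been run. These gains are for a pooled mean; they have not been worked out for country or subgroup results.

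**What to change.** 1. Estimate mean QALYs with a calibrated or post-stratified two-phase estimator. Calibrate to a short list of well-recorded cohort variables: hospital, age, sex, wealth quintile, and readmission and death by day 90. Where the date of death is available, use days alive as well. Do this within country, because the tariffs differ.
2. Use a two-phase variance and show the unweighted sub-sample mean alongside.
3. Treat mean patient cost the same way for consistency, without expecting much narrower intervals.
4. Include death and readmission, not only baseline variables, in the imputation model for costs and HRQoL.
5. Do not calibrate on CKD, which is incompletely ascertained.
6. State who received the EQ-5D. Only if it was in fact given outside the third, analyse HRQoL in everyone who has it.

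The cost is analysis wording and standard survey methods, with no new data. The downside is a somewhat more complex analysis, since the two-phase variance must be combined with multiple imputation, and some loss of the gain where day-90 status is missing.

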### Analysis

**
*Phase 1 A: Prospective longitudinal cohort study - quantitative statistical analysis*.** We will report the study in accordance with STROBE guidelines. A CONSORT diagram will summarise participant enrolment and follow-up. We will report descriptive statistics, including N (sample size of analysis population), n (sample size of analysis population without missing values). For continuous data we will report the mean and standard deviation for normally distributed data, or median and interquartile range for data that are not normally distributed. The proportion of observed levels will be reported for all binary and categorical measures alongside corresponding exact, binomial exact 95% confidence intervals (CIs) for proportions when appropriate. Results will be disaggregated by sex. Where appropriate, we will use multiple imputations using chained equations for missing data.

Will provide in-depth baseline epidemiologic and clinical management data across the different sites. Similarities and differences across sites will be recorded. Analysis will include evaluation of the association between clinical management and patient outcomes. Univariate and multivariate strength of association between variables and patient outcomes will be tested by logistic regression modelling.

Prevalences will be given as a proportion with 95% confidence intervals of the population estimate. Combinations of more than one will be assessed for their “joint prevalence” in order to understand multimorbidity disease clusters.

**
*Phase 1B: Health economic*.** Principle components analysis (PCA) will be used to construct wealth scores using individuals’ asset and other data, and wealth quintiles in the study population. Additionally, participants will be assigned to quintiles in reference to most recent DHS survey, allowing socioeconomic assessment of the study population relative to the national population.

Patient costs will be estimated for each individual patient including any costs incurred by their guardians in accompanying them to hospital or subsequent health care visits. Indirect costs (
*e.g.*, lost time for paid or unpaid work, including housework) will be estimated based on the number of days of reported inability to work multiplied by the pre-disease wage given by patients during their baseline interview. The patient pathway model will be parameterised with unit costs and used to estimate individual patient and health system costs for a set of the most frequently observed multimorbidity combinations and patient types. Capital costs extending beyond one year will be annualised over their expected lifespan. Results will be presented as means and 95% confidence intervals. Deterministic and probabilistic sensitivity analyses will be conducted to test the robustness of the results. Multiple logistic regression will be used to compare patient costs by multimorbid condition(s) and wealth quintile to identify any significant differences. Additionally, we will examine the relationship between patient costs and age and sex. Change in HRQoL, expressed as QALYs, between admission, day 30 and day 90 interviews will be estimated using the area under the curve method. QALYs will be calculated according to the most relevant available tariff based on both geographical proximity and economic context. In our study we will use Uganda’s tariff for Tanzania, and Zimbabwe’s tariff for Malawi. Updated tariffs will be used if these become available before the analysis. The QALY calculations will also consider mortality during follow-up by attributing the lowest value from each value set (which corresponds to death), from the date of death until the end of the follow-up period. Missing patient cost or HRQoL data will be imputed using multiple chained imputations modelling with a predictive mean matching algorithm and relevant baseline variables.

Health economic analysis will be performed in Stata v15.4 and Excel.

**
*Phase 1 C: Situation analysis*.** Transcription and translation will be performed in line with local standard procedures. For accuracy, during the first 10 transcriptions a researcher will read the transcribed interviews and focus groups while listening to the audio recordings, and then check translations. Further checks will depend on the quality of these initial evaluations.

For in-depth interviews and focus group discussions, all data collected will be transferred to a qualitative data analysis software package (NVivo), to enable analysis. Data will be analysed following broad deductively defined themes and inductively derived sub-themes. We will employ a combination of thematic and framework coding to compare perspectives between different stakeholders. Two researchers will undertake initial coding of a small number of transcripts, and then discuss and agree themes for further coding. Analysis will be performed concurrently with fieldwork using an iterative approach to identify emerging themes that can be clarified or explored further through later data collection. Data will be triangulated between methods and participant groups to cross-check information and provide a more comprehensive analysis.

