### Objectives

The primary objectives of this mixed methods (clinical, health economics and qualitative) study are:

*Clinical:* Determine the prevalence of multimorbid disease in adults admitted to hospital with acute medical conditions in Malawi and Tanzania.

*Health Economic:* Measure economic costs incurred and changes in health-related quality of life between admission and 90 days post admission.

*Situation analysis:* Describe current care for multimorbidity, enabling and hindering factors to the delivery of patient centred care.

We aim to use the findings to inform the development and design of a randomised controlled trial.

The secondary objectives are:

*Clinical:*

1.Measure prevalence of important pre-selected individual conditions, including chronic non-communicable (hypertension, diabetes mellitus and chronic kidney disease) and communicable (HIV infection) conditions.2.Measure hospital readmission rate 30 and 90 days after admission.3.Measure survival 30 and 90 days after admission.4.Measure a composite of readmission free survival 30 and 90 days after admission.5.Measure markers of disease control 90 days after admission.6.Measure the rate of end-organ damage (such as cerebrovascular accident and myocardial infarction).

*Health Economic:*

1.Disaggregate economic costs from patient and health system perspectives and sub-analyse according to the presence of multimorbidity and other socio-economic factors.2.Model how patients with different multimorbidity incur costs as they pass through the health system.3.Analyse changes in Health-related Quality of Life according to presence of different diseases.4.Estimate the potential cost-effectiveness of a selected intervention to improve diagnosis and treatment for people with multimorbidity.

*Situation Analysis:*

1.Describe healthcare pathways for adults during and after acute medical admission using structured observational data during patient admission.2.Qualitatively describe (i) patients’ level of health literacy related to their own conditions and (ii) healthcare engagement for patients with multimorbidity using key-informant interviews.

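### The only stated rule for binary outcomes would, unless data are imputed, estimate 30- and 90-day survival and readmission-free survival among participants with known status, which overstates mortality even when loss after discharge is random

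*Protocol article*

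**What the plan says.** The secondary clinical objectives include "Measure survival 30 and 90 days after admission" and "Measure a composite of readmission free survival 30 and 90 days after admission".

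Under Data sources and measurement, "Clinical outcomes will also be ascertained at hospital discharge, 30 days and 90 days as" introduces two outcomes: death and readmission. Death is described as "Death (coded from all available records".

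The Phase 1 A part of the Analysis section then gives:

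- a summary rule: "The proportion of observed levels will be reported for all binary and categorical measures alongside corresponding exact, binomial exact 95% confidence intervals", with the intervals qualified as applying when appropriate;
- two sample sizes to be reported: the analysis population N, and "n (sample size of analysis population without missing values";
- a missing-data sentence: "Where appropriate, we will use multiple imputations using chained equations for missing data";
- a model for outcomes: "Univariate and multivariate strength of association between variables and patient outcomes will be tested by logistic regression modelling".

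The section names no time-to-event or other censoring-aware method. The imputation sentence does not say whether survival is covered or which variables enter the model.

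**The concern.** Status at day 30 or day 90 is not missing evenly across the cohort. Someone who dies on the ward is seen by the study team and has a known outcome. Someone discharged alive has to be reached by telephone, home visit or clinic, and may not be. Dropping those with unknown status therefore removes people who have already survived the admission, while the in-hospital deaths all stay in the numerator. The loss does not have to be related to prognosis for this to bias the result.

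Two secondary clinical objectives are affected. The article says that the findings will inform the design of a randomised trial and that Phase 2 includes cost-effectiveness modelling, so these rates may be used again.

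**Working it through.** **The plan's own figure.** The article gives no expected mortality and no expected loss after discharge. The nearest figure is the dropout allowance under Sample size, 1544 raised to 1600: (1600 - 1544)/1600 = 56/1600 = 3.5% of those enrolled. It was set for the prevalence estimate.

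**Assumed inputs (not in the article).** h = in-hospital mortality, 10% or 20%. q = mortality from discharge to day 90, 10%. l = random loss among those discharged alive, 10% or 20%. All in-hospital deaths are taken as known.

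**Formulas.**

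- True mortality = h + (1-h)q
- Known-status mortality = [h + (1-l)(1-h)q] / [h + (1-l)(1-h)]
- Difference = (1-h)(1-q) × l × h / [1 - l(1-h)]

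The difference is positive whenever h > 0, l > 0 and q < 1.

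**Example, h = 20%, l = 20%.** True mortality = 0.20 + 0.80 × 0.10 = 0.280. Known-status mortality = (0.20 + 0.064)/(0.20 + 0.64) = 0.264/0.840 = 0.314.

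| h | Loss | True | Known status | Excess (points) | 95% half-width (points) |
|---|---|---|---|---|---|
| 10% | 3.5% of enrolled | 19.0% | 19.3% | 0.3 | 2.0 |
| 10% | 10% of discharged | 19.0% | 19.9% | 0.9 | 2.1 |
| 10% | 20% of discharged | 19.0% | 21.0% | 2.0 | 2.2 |
| 20% | 3.5% of enrolled | 28.0% | 28.7% | 0.65 | 2.3 |
| 20% | 10% of discharged | 28.0% | 29.6% | 1.6 | 2.3 |
| 20% | 20% of discharged | 28.0% | 31.4% | 3.4 | 2.5 |

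Half-widths are 1.96 × sqrt[p(1-p)/n], with p the known-status proportion and n the number with known status out of 1600. In the 3.5% rows the known-status denominator is 0.965; for h = 20% this gives (0.20 + 0.0765)/0.965 = 0.2865.

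**Simulation.** In 2000 simulated cohorts of 1600, with 15% in-hospital mortality, 15% post-discharge mortality and 20% random loss, the truth is 27.8%. The known-status proportion averaged 30.4% and its exact 95% interval covered the truth in about 44% of cohorts. Combining observed in-hospital mortality with post-discharge mortality among those followed returned 27.8%.

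**Readmission-free survival.** The same formula applies with q as the risk of death or readmission after discharge. A larger q makes the difference smaller. With q = 20% (assumed), it is 0.8 to 1.4 points at 10% loss and 1.8 to 3.1 at 20%, for h of 10% to 20%.

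**What imputation does.** Take h = 20%, q = 10%, l = 20%, so that 16% of the cohort is missing. If the imputation model does not know that these people left hospital alive, and its baseline variables carry no information on it, they are assigned the known-status risk and the estimate stays at 31.4%. If discharge status is in the model, they are assigned 10%: 0.264 + 0.16 × 0.10 = 0.280, the true value.

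**Direction under informative loss.** With 10% of post-discharge survivors lost, the bias is zero when the lost share of post-discharge deaths is 0.10 × true mortality / [(1-h)q]. For h = 10% this is 0.10 × 0.19/0.09 = 21%. For h = 20% it is 0.10 × 0.28/0.08 = 35%. Above these shares, mortality is understated.

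**The case against.** The strongest reply is that the article does not commit to a known-status analysis of survival. The rule is a general descriptive one, its intervals carry a qualifier, both N and n are to be reported, and multiple imputation appears in the same paragraph. The choice of estimator for a secondary outcome may also sit in a statistical analysis plan that is not shown. A reader might infer that survival is definitely to be reported among those with known status; the text does not support that, and the point is limited to what happens unless the data are imputed. What remains is that the stated rule covers all binary measures, that the only model named for outcomes is logistic regression, and that neither handles censoring. Imputation is neither promised for survival nor tied to discharge status.

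Other replies also have force:

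- **Size.** Loss may be small. Telephone contactability is an entry criterion, the day-30 contact can be a home visit, deaths are sought in all available records, and contact may continue to about 12 months. At 3.5% dropout the excess is well inside the interval. In the table it exceeds the half-width only at 20% loss with 20% in-hospital mortality.
- **Direction.** A reader might infer that mortality must be overstated. That is certain only for random loss.
- **Completeness of in-hospital deaths.** Under deferred consent, a patient who dies before consent or proxy assent might be excluded, so in-hospital deaths are almost always known, not always.
- **Dates.** The article uses the date of death for quality-adjusted life years, an analysis planned in the one-third sub-sample. It does not state that a readmission date is recorded.
- **Consequence.** A reader might infer that an inflated event rate would mislead the power of the later cluster trial. The article does not give that trial's outcome or say that these proportions will set its event rate.

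**Conclusion.** The point holds in a limited form. Applied to 30- and 90-day survival and readmission-free survival without suitable imputation, the stated rule overstates mortality under random post-discharge loss. For 90-day mortality, the excess is about 0.9 to 1.6 points at 10% loss and 2.0 to 3.4 points at 20%, given assumed in-hospital mortality of 10-20% and post-discharge mortality of 10%. At the 3.5% implied by the sample size it is 0.3 to 0.65 points and would not matter much. If post-discharge deaths are lost more often than survivors, the bias shrinks and can change sign, and the known-status proportion is then unreliable in a different way. The documents do not support saying that the plan fixes a biased analysis, or that the bias will exceed the confidence interval. They do support stating the estimator for these two objectives now.

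**What to change.** Add a short statement to the Phase 1 A analysis:

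1. **Survival at 30 and 90 days:** Kaplan-Meier from admission, with every enrolled participant entered and censoring at the last date known alive, reported with a 95% confidence interval. First confirm that dates of death are held for the whole cohort.
2. **Readmission-free survival:** the same method if event dates are recorded. If they are not, either combine in-hospital event status with the post-discharge risk among those followed, or use multiple imputation that includes discharge and day-30 status. Imputed results should be pooled by Rubin's rules, because an exact binomial interval does not apply to imputed counts.
3. **Known-status proportion:** keep it as descriptive only.
4. **Sensitivity analysis for informative loss:** include the case where deaths among people lost to follow-up are found from records while lost survivors are censored early, since Kaplan-Meier would then also overstate mortality.

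The cost is a little extra analysis work and a main estimate that relies on non-informative censoring. For survival, no new data should be needed if dates of death are held. The article reports that the study is in follow-up, the code is still under development and no analysis has been done, so the change can be made before results are seen.
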